## Abstract

**Background::**

Schools have become a key figure for the promotion of health and obesity
interventions, bringing the development of critical awareness to the
construction and promotion of a healthy diet, physical activity, and the
monitoring of the nutritional status in childhood and adolescence.

**Objectives::**

To describe a study protocol to evaluate the effectiveness of an intervention
designed to improve knowledge of food choices in the school environment.

**Methods::**

This is a cluster-randomized, parallel, two-arm study conducted in public
elementary and middle schools in Brazil. Participants will be children and
adolescents between the ages of 5 and 15 years, from both genders. The
interventions will be focusing on changes in lifestyle, physical activities
and nutritional education. Intervention activities will occur monthly in the
school’s multimedia room or sports court. The control group arm will receive
usual recommendations by the school. The primary outcome variable will be
anthropometric measures, such as body mass index percentiles and levels of
physical activity by the International Physical Activity Questionnaire.

**Results::**

We expect that after the study children will increase the ingestion of fresh
food, reduce excessive consumption of sugary and processed foods, and reduce
the hours of sedentary activities.

**Conclusion::**

The purpose of starting the dietary intervention at this stage of life is to
develop a knowledge that will enable for healthy choices, providing
opportunities for a better future for this population.

## Introduction

The increased prevalence of obesity and its complications reinforces the global need
for improved prevention strategies.^1-3^ In Brazil,
population-based surveys indicate that overweight was present in 6% of children
between 5 and 9 years in 1974-1975, rising steeply to 34.8% in 2008-2009.^4^ Globally, overweight in children
increased 47.1% over the past 20 years.^5^ In 2010, it was estimated that overweight and obesity were
responsible for 3.4 million deaths worldwide.^6^ Chronic diseases remain a public health challenge in Brazil.
The medical costs associated with diseases related to overweight and obesity are
substantial in Brazil, reaching nearly US$ 2.1 billion annually.^7^

Overweight in children and adolescents generates great concern because it is a risk
factor for the development of hypertension, type 2 diabetes mellitus, dyslipidemia
and other cardiovascular risk factors,^8,9^ which, if not
prevented or treated at an early age, tend to persist during adulthood.^10^

Nutritional intervention studies have shown a positive effect on preferences for
healthy foods and a decrease in daily consumption of sugary drinks.^11,12^ Permanent changes in diet quality, energy intake and
physical activity demand preventive actions.^13^ On that account, promotion of a healthy diet, physical
activity, and monitoring of the nutritional status in childhood and adolescence are
essential elements in public health. Being an educational environment that
contributes to build personal values, schools become a key figure for health
promotion and obesity interventions, bringing the development of critical awareness
to the construction and modification of eating habits.^14,15^

A number of international agencies, such as the Centers for Disease Control and
Prevention (CDC) and the Institute of Medicine (IOM), launched campaigns with
guidelines for health promotion in schools aiming to address the epidemic of obesity
and its consequences.^16-18^ In Brazil, the School Health
Program is designed to promote the comprehensive health care of public school
students and is structured in four blocks that seek to: assess health conditions;
perform actions of prevention and promotion of health conditions; promote continuing
education for professionals and the young; present evaluation and monitoring of
health conditions of the students. The responsibility for planning and carrying out
these actions is upon the primary care health team, and the objective is to
integrate the educational system and the Brazilian Unified Health System
(SUS).^19^ However, this
government action does not have coverage of all schools in the country yet.

In order to implement educational interventions in a large scale, it is important to
adequately test their effectiveness. It is also important to look for simple and
low-cost alternatives that can reach the largest possible number of schools.
Improving the knowledge about food choices may be an important basis for children to
acquire and maintain a healthy lifestyle from an early age, and possibly to sustain
these healthy habits in subsequent stages of life.

Thus, the purpose of this study protocol is to evaluate the effectiveness of an
intervention designed to improve knowledge of food choices in the school
environment.

## Methods

This protocol is reported according to the SPIRIT (Standard Protocol Items:
Recommendations for Interventional Trials) statement.

### Study design

#### Overview

This is a cluster-randomized parallel two-arm study conducted in Brazil. The
units of observation are individual children, and the units of randomization
are schools. Randomization will be performed at the school level to avoid
contamination. After the baseline assessment, enrolled schools are
randomized to one of two study arms: the intervention arm focusing on
changes in lifestyle, and the control group arm, that receives usual
recommendations by the health care team. A summary of the study design,
interventions and timelines is shown in Figure 1.

**Figure 1 f1:**
[figure not shown]
Flowchart of the study phases (enrolment, intervention
allocation, and fnal assessments).

The primary outcome for the participants is change in body mass index (BMI =
kg/m^2^), and the secondary outcomes are behaviors related to
healthy eating, increased preferences for fruits and vegetables, increased
physical activity and reduced screen time. The Institutional Research Ethics
Committee approved the protocol for the study, which is registered in the
Brazilian Registry of Clinical Trials, Register Number RBR-97bztb, and named
“Intervention program for health promotion in schools of public elementary
school in the state of Rio Grande do Sul: randomized clinical study”. The
Universal Trial Number of this study is U1111-1155-7731.

#### Inclusion criteria

Children between the ages of 5 and 15 years, from both genders, enrolled in
the public schools participating in this study, attending from the 1st to
the 9th grades of the elementary and middle school will be eligible for the
study (Table 1). The child and
parent(s) or legal guardian(s) are required to sign the assent term and the
informed consent.

**Table 1 t1:** Inclusion criteria and assessment methods.

Inclusion criteria	Assessment method
Age 5-15 years	In person screening
Enrolled in one of the participant schools, attending a course from the 1^st^ to the 9^th^ grade of the elementary and middle school.	Electronic school review
Agreeing to participate in all the meetings of the study	In person screening

#### Exclusion criteria

Children are excluded if they have conditions or other circumstances that
could interfere with participation in the measurements or the interventions
or if the parent does not give or is unable to give consent or the child
does not assent. Participants are also excluded if they do not complete
baseline assessments in 3 weeks.

#### Screening and recruitment

The screening and recruitment activities will be developed during the course
of 4 weeks. During the first week, the school electronic files of student
enrollment will be consulted to identify potential participants (the
eligibility criteria can be seen in Table 1). During the following two weeks, recruitment letters will be
sent to the student's guardians, with explanation of the study and attached
Informed Consent Form. During the fourth week, individuals who agree to
participate in the study will undergo anthropometric assessment, provided
that there is no impediment for physical evaluation.

#### Randomization

Cluster randomization will be performed with distribution of two schools for
the control group and two schools for the intervention group. A
biostatistician who does not have direct contact with study participants
will generate the random allocation sequences using a computerized random
number generator. After the inclusion of each cluster, the allocation of
that particular cluster will be provided to the study coordinator. Due to
the characteristics of the intervention, it is not possible to mask
participants or interventionists to group assignment. There will be no
crossover between study arms, but the intervention will be offered to the
control group at the end of the study, if proved to be effective.

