#### Sample size

The sample size was calculated to detect a difference in 0.2 kg/m^2^
on BMI, with a standard deviation of 0.05, statistical power of 90% and
alpha error of 0.05. An estimate of mean 19 kg/m^2^ is used as
obtained from our pilot study. A number of 99 participants per group was
estimated using these parameters. To compensate for losses, the sample size
will be increased by 10%.

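### The 99 per group and 90% power are computed as for individually randomised children although only four schools are randomised, so the 90% is unsupported; the size of the shortfall depends on an SD that must first be reconciled

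*Protocol article*

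**What the plan says.** The Overview of the protocol article separates the two units: children are observed, but "the units of randomization are schools". The Randomization section fixes the number: "Cluster randomization will be performed with distribution of two schools for the control group and two schools for the intervention group".

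The Sample size section starts from a BMI difference of 0.2 kg/m², "with a standard deviation of 0.05", power 90%, alpha 0.05 and a pilot mean of 19 kg/m². It concludes: "A number of 99 participants per group was estimated using these parameters". The only later adjustment is a 10% increase for losses.

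Planned data analyses names generalized estimating equations (GEE) for the adjusted analysis of primary and secondary outcomes. The primary outcome in the Overview is change in BMI.

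**The concern.** When schools are randomised, children in the same school tend to resemble one another, and the information about the treatment effect is limited by the number of schools as well as the number of children. A size calculation for this design needs an ICC, a cluster size and the number of clusters. The Sample size section lists its parameters and says that 99 came from them, and none of these three is among them. This is therefore not a detail that the article has merely shortened: the calculation is stated, and it is one for individually randomised children.

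The trial sets out to evaluate effectiveness, and the control schools are to be offered the programme only if it proves effective. A 90% power claim that the design does not support gives a non-significant result more weight as evidence of no effect than it could carry. A significant result would rest on two schools against two.

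**Working it through.** **Inputs from the protocol article.** Difference 0.2 kg/m², SD 0.05 as printed, power 90%, alpha 0.05 (taken as two-sided), 99 per group, two schools per arm. Hence m = 99/2 = 49.5 analysed children per school.

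**Assumption.** The document gives no ICC. The values 0.01, 0.02 and 0.05 are assumed, with 0 as a reference.

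**Step 1: the plan's own figure.** n per group = 2(1.960 + 1.282)² × SD²/difference² = 21.01 × SD²/0.04.
- SD 0.05: 21.01 × 0.0025/0.04 = 1.3, so 2 per group (about 3 with the t correction). The stated 99 is not reproduced.
- Solving for the SD that gives 99 at 90%: √(99 × 0.04/21.01) = 0.434.
- SD 0.5 also gives 99, but at 80% power: 2(1.960 + 0.842)² × 0.25/0.04 = 98.1, rounded up. At 90% it needs 132.

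Both routes to 99 are formulas for individual randomisation, with no clustering term.

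**Step 2: add clustering.** Design effect DE = 1 + (m − 1) × ICC. With two schools per arm, SE = SD × √(DE/m). Power by the z approximation is Φ(0.2/SE − 1.96). A school-level t test has 4 − 2 = 2 degrees of freedom (critical value 4.303), and its power is the upper tail of a noncentral t with noncentrality 0.2/SE. Example at SD 0.434 and ICC 0.02: DE = 1 + 48.5 × 0.02 = 1.97; SE = 0.434 × √(1.97/49.5) = 0.087; noncentrality 0.2/0.0866 = 2.31.

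| ICC | DE | Effective n per arm | Power, z, SD 0.434 | Power, 2 df, SD 0.434 | Power, 2 df, SD 0.5 | 95% CI half-width, 2 df, SD 0.434 |
|---|---|---|---|---|---|---|
| 0 | 1.00 | 99 | 90% | 43% | 35% | 0.27 |
| 0.01 | 1.49 | 67 | 76% | 33% | 27% | 0.32 |
| 0.02 | 1.97 | 50 | 64% | 27% | 22% | 0.37 |
| 0.05 | 3.43 | 29 | 42% | 18% | 15% | 0.49 |

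Half-widths are 4.303 × SE in kg/m², and all exceed the 0.2 target.

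**Step 3: would more children in the same four schools help?** As m grows without limit, SE tends to SD × √ICC. At SD 0.434 the ceiling on 2 df is 66%, 43% and 23% for ICC 0.01, 0.02 and 0.05. Below an ICC of about 0.005 the ceiling passes 90%: at ICC 0.001, 300 children per school give 91%.

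**Step 4: the printed SD taken literally.** With SD 0.05 the target is 0.2/0.05 = 4 SDs. The 2-df test then has about 100% power at ICC 0.05, 97% at 0.2 and 92% at 0.3.

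**A limit that needs neither SD nor ICC.** Four schools split two and two allow 6 allocations, so a two-sided randomisation test cannot give a p-value below 2/6 = 0.33. The protocol does not plan this test; the figure only shows how little four units can carry.

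**The case against.** **The printed SD gives ample power.** Step 4 shows that this is true on its face. A reader might infer that the trial as printed has well under half of its claimed power, and the document does not support that reading: the shortfall appears only once the SD is set to a value consistent with 99. But the printed SD cannot defend the calculation, since it leads to 2 or 3 children per group. What stands is that the SD comes first and every shortfall figure is conditional on it.

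**GEE is planned, not a 2-df t test.** This is fair. The design-effect-only figures (76%, 64%, 42%) are the lenient reading, and the 2-df figures are not the power of a test that the protocol names. Both belong in the account. GEE does not repair the size calculation, however. It acts in the analysis, and its usual robust standard errors are unreliable with four clusters, so the z figures are optimistic.

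**The ICC is assumed.** Correct. The outcome is change in BMI, baseline adjustment could alter the ICC and the SD, and school size is not fixed at 50. Any positive ICC lowers power, and on 2 df there is a shortfall at SD 0.434 and 49.5 children per school even at ICC 0. The size remains a range.

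**More children could be recruited.** A reader might infer that extra children in these four schools can never restore 90%. Step 3 shows that this is too strong: it holds on 2 df over the assumed ICC range, not below about 0.005. By the z approximation, the ceiling with unlimited children is 99.6%, 90.3% and 54% at ICC 0.01, 0.02 and 0.05.

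**Conclusion.** The point holds in conditional form. The Sample size section treats children as if individually randomised, while four schools are randomised, so the 90% power is unsupported. That conclusion needs no assumed ICC or SD.

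The size of the shortfall does need them. At SD 0.434 (implied by 99 per group at 90%), 49.5 children per school and ICC 0.01 to 0.05, power lies between 76% and 42% if only the design effect is counted, and between 33% and 18% if the few schools are also reflected in the degrees of freedom. No single figure can be called the trial's power until the SD is reconciled and an ICC range is stated.

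**What to change.** In the Sample size section:
1. Reconcile the SD with the stated 99 per group and 90% power, and say whether it refers to BMI or to change in BMI.
2. Withdraw the 90% power claim.
3. Restate the power, or the expected 95% CI half-width (about 0.32 to 0.49 kg/m² at SD 0.434), using 1 + (m − 1) × ICC and degrees of freedom suited to four clusters, over a stated ICC range.

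In Planned data analyses, cluster the GEE on school and use a small-sample correction. Present the BMI comparison as estimation with its interval, not as a test with 90% power.

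The cost is rewording and a much less favourable stated power; no schools or children are added. If the sponsor wants to keep a 90% claim, the alternative is more schools: at SD 0.434 and about 50 children per school, roughly 5, 6 or 8 per arm for ICC 0.01, 0.02 or 0.05. That is a far larger change and is not required to correct the text.

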#### Assessments

Measures are conducted at baseline (month one) and post-treatment (month
9).

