#### Intervention description

Intervention activities will occur monthly in the school multimedia room or
sports court (Table 2). All
activities will be offered in different school shifts and schedules so that
all students in all classes can participate.

**Table 2 t2:** Description of intervention activities

Intervention	Type	Description	Moment
Presentation of the program to students, parents and teachers.	Seminar	A seminar approaching the following topics will be conducted: epidemiological data on obesity and noncommunicable disease risk factors; dyslipidemia tracking; importance of school intervention; presentation of the activities that will be developed during the school year; reading and clarification of the Informed Consent Form.	1st Month
Knowing what we eat.	Seminar	The seminar will succinctly address the composition of food, approaching macronutrients, fibers and food groups. As a task for the week, each class should study the vitamins and prepare a poster on that topic during class time. As a homework assignment, all students should create, with the help of parents, a list of five fruits and six vegetables they like to eat. Three of them should be cooked vegetables and three of them raw vegetables.	2nd Month
The importance of water.	Seminar	The seminar will address the importance of water in our health and the consequences of high consumption of sugary drinks. Soft drink consumption has increased in recent decades in Latin America, and that is being referred as a contributor to the population weight gain. Many schools sell soft drinks in the cafeteria and some children end up consuming them daily without parents' knowledge.The “Week without soda” challenge will be launched, in which children, parents and teachers will commit to spend a week without drinking soft drinks, which will require the family interaction and commitment for the accomplishment of the goal.	3rd Month

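### Table 2 puts explanation of the consent form inside the first intervention seminar, which conflicts with the stated order of consent, baseline and then randomisation; the allocation-release rule does not settle the order

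*Protocol article*

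**What the plan says.** All references are to the protocol article.

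- **Overview:** "After the baseline assessment, enrolled schools are randomized to one of two study arms".
- **Screening and recruitment:** a single four-week route for all schools. School files are searched in week 1, letters with the consent form go to guardians in the next two weeks, and those who agree have anthropometry in week 4. No seminar is mentioned.
- **Randomization:** two schools per arm. A biostatistician without participant contact generates the sequence, and "After the inclusion of each cluster, the allocation of that particular cluster will be provided to the study coordinator". Participants and interventionists are not masked.
- **Assessments:** baseline is in month one, the final assessment in month 9.
- **Intervention description, Table 2, 1st Month:** a seminar for students, parents and teachers whose content includes "presentation of the activities that will be developed during the school year; reading and clarification of the Informed Consent Form".
- **Usual care comparator:** control participants get no guidance from the study, only what school and health authorities usually provide.

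**The concern.** In a cluster trial, randomising schools protects the comparison only if the children who enter do so independently of their school's arm. If some families decide on consent after the arm is known, and after a session that presents the programme, the two arms may enrol differently motivated families. Randomisation does not guard against this, and intention-to-treat analysis does not address who was enrolled. With two schools per arm, covariate adjustment cannot be relied on to repair it.

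Several entry rules could work differently by arm if applied after allocation. Table 1 requires willingness to attend every study meeting, which is a heavier commitment where monthly activities are planned. The exclusion criteria cover refusal of consent, circumstances that interfere with measurements or interventions, and baseline not completed within 3 weeks. The blind adjudicator named under Planned data analyses protects outcome evaluation, not enrolment.

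**Working it through.** **1. The order of steps, section by section**

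| Section | Order stated or implied |
|---|---|
| Overview | baseline, then randomisation |
| Screening and recruitment | consent form by letter, then agreement, then anthropometry |
| Randomization | inclusion of a school, then release of its allocation; baseline not mentioned |
| Table 2, 1st Month | consent form explained within an intervention activity |

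The first two rows combine to consent, baseline, randomisation. The fourth does not fit, because an activity confined to one arm cannot be delivered until the arm is known. The third fits either order, depending on what inclusion means.

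**2. Possible readings of the Table 2 row**

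- *After allocation, and consent is decided there.* This contradicts the Overview and opens the recruitment-bias route.
- *After allocation, as a re-reading for families who have already consented.* There is no recruitment bias, but the row does not say this.
- *Before allocation, in all four schools.* The order is then sound, but the session is not an intervention activity. Control schools would also hear its material on obesity and risk factors, which sits badly with the no-guidance statement for controls.

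Nothing in the text chooses between these, and each needs a change of wording.

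**3. Timing within month 1**

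The article does not say how the four recruitment weeks map onto month one. Two assumptions show the range. If they are the same four weeks, anthropometry in week 4 leaves only that week for measurement, randomisation and seminar. If week 4 of recruitment opens month one, about 4 - 1 = 3 weeks remain for the seminar. So baseline followed by the seminar is possible but not assured. Only anthropometry has a stated week; the diet, physical activity, screen-time and knowledge questionnaires have none.

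**4. Sequential release under 2:2 (secondary)**

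- Possible sequences for four schools: 4!/(2! x 2!) = 6.
- After three releases the fourth arm is always known: 6/6.
- After two releases the last two are known only when the first two match: 2/6 = 1/3.
- Expected correct guesses for someone who always picks the arm with more places left: 1/2 for the first school; 2/3 for the second; (1/3 x 1) + (2/3 x 1/2) = 2/3 for the third; 1 for the fourth. The total is 2.83 of 4, against 2 by chance.

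**5. Size of a possible bias**

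The document gives no input for this. If a share p of the intervention sample were extra motivated families whose BMI change is lower by d, the bias is p x d. Purely as an assumption, p = 0.15 with d = 0.3 to 0.5 kg/m2 gives 0.045 to 0.075 kg/m2. Against the 0.2 kg/m2 target under Sample size, that is 22.5% to 37.5%. With p = 0 or d = 0 the bias is zero. These values show the mechanism only and are not carried into the conclusion.

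**The case against.** The strongest reply is that the Overview and Screening and recruitment already give a clear, arm-neutral order, and that one phrase in a table of activities should not override them. Inclusion of a cluster can naturally mean that its enrolment and baseline are complete. Explaining a form is not the same as collecting signatures. Figure 1, which charts enrolment and allocation, is not available here and may show the order.

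Much of this stands, and it rules out several stronger readings that a reader might infer:

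- *That the Randomization section contradicts the Overview.* It does not; it is ambiguous.
- *That control families receive only a letter.* The article does not describe how consent is explained in control schools. The absence of an equivalent session is inferred from Table 2 being the intervention table and from the no-guidance statement.
- *That baseline data are contaminated by the seminar.* The order within month 1 is not given. Measured weight and height are unlikely to be affected; self-reported questionnaires could be, if taken afterwards.
- *That predictability of the last school biases the trial.* It matters only if someone can choose schools or children knowing the next allocation. If all four schools are enrolled before any release, it has little effect on which schools enter.
- *That the bias is a known fraction of the target effect.* The illustrative d is 1.5 to 2.5 times the whole target (0.3/0.2 and 0.5/0.2), and the result follows entirely from the inputs chosen.

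The reply does not remove the Table 2 wording. It places consent explanation and "presentation of the activities that will be developed during the school year" in one session, in the intervention arm, in the baseline month, and no other section explains it.

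**Conclusion.** The point holds as an internal conflict between Table 2 and the order given by the Overview with Screening and recruitment. The Randomization section should settle the matter and does not. The consequence is a risk of differential recruitment, not a demonstrated occurrence, and its size cannot be derived from the document. The conclusion rests on one assumption: that activities listed in Table 2 are delivered only in intervention schools, as its title and the comparator description indicate. Predictability under sequential release is arithmetically certain for the fourth school but secondary. The severity is should-fix: the ambiguity concerns comparability of the arms and could not reliably be repaired in analysis, but the benign readings remain open.

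**What to change.** State one sequence, in the same terms, in the Overview, Screening and recruitment, Randomization and Table 2:

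1. Enrol all four schools and give the same consent information in each.
2. Complete consent and all baseline measures, questionnaires included, in all four schools.
3. Have the biostatistician release all four allocations together.
4. Hold the month-1 intervention seminar only after that.

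Move the consent step out of Table 2 into the common recruitment phase, and define inclusion of a cluster as completion of step 2.

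Before recruitment, the cost is revised wording and coordination of dates across four schools, with no extra participants. The Discussion calls the trial ongoing, so re-sequencing may no longer be possible. In that case, document the actual order of consent, baseline and allocation in each school. Report the numbers approached, consented and excluded, with baseline characteristics, by school and arm. That costs some record retrieval and an extra table, and it lets readers judge the risk without removing it.
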